### Assessment of other variables

Data on dietary habits and dietary intakes of participants will be obtained using standard questionnaires in the run-in period. In addition, demographic data, and medical history will be examined using a general information questionnaire during this period. Moreover, participants will be asked to provide three 24-h food recalls throughout this period.

Anthropometric measures including weight, height, and waist circumference (WC) will be measured and BMI (weight (kilograms) divided by the squared height (meters)) will be calculated at the study beginning and end. Participants will be weighed with minimum clothing and without shoes, to the nearest 100 g using a digital scale. Standing height will be measured without shoes, to the nearest 0.5 cm using a standard stadiometer. WC will be measured using a strip meter at the mid-distance interval between the super elliptic bone and the last rib, to the nearest 0.5 cm. In addition, blood pressure will be measured twice at the right arm using a mercury barometer calibrated by the Institute of Standardization and Industrial Research, with a 15- min interval in between measurements, while the patient is sitting quietly for 5 min. The average of two measurements will be analyzed for the participants’ systolic and diastolic blood pressure. Moreover, participants’ physical activity will also be estimated at beginning and end of the study, using 3-day physical activity records.

Participants’ sublingual body temperature will be measured twice with a 15-min interval between measurements, using a standard mercuric thermometer in a room with a temperature of 24–26 °C. The mean of the two measurements will be analyzed as the participant’s body temperature. The mean of two manual counts of pulse rate from the left wrist within 1 min (with a 5-min interval between counts) will be analyzed as the pulse number per minute. In addition, the severity of IBD will be examined using the 9-point partial Mayo score [14], participants’ quality of life assessed by the IBDQ-9 self-administrated questionnaire [19], disabilities due to IBD assessed by the IBD Disability Index (IBD-DI) questionnaire [20], and depression and anxiety assessed by the HADS Hospital Scale [21]. In addition, participants’ psychological stress will also be examined using the General Health Questionnaire (GHQ) [22].

### Study sample size calculation

By considering a type I error of 5% (α = 0.05) and type II error of 20% (β = 0.20, power = 80%) and the primary outcome variable of expected difference between the intervention and control groups in mean fecal calprotectin, calculated based on the two sided *t* test, we calculated the required sample size using the following formula:
$$ n=\frac{{\left({\mathrm{Z}}_{1-\frac{\alpha }{2}}+{\mathrm{Z}}_{1-\beta}\right)}^2\times \left({S_1}^2+{S_2}^2\ \right)}{\left({\upmu_1}^2-{\upmu_2}^2\right)} $$

(S1= 25.88, S2= 21.99, μ1= 26.6, μ2= 4)

Based on this formula and allowing for 10% drop-out in each group, we will need a sample size of 15 persons for each group.

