### Assessment of study outcomes

#### Primary outcomes

The main primary outcomes in the current study would be fecal calprotectin and lactoferrin as well as gut microbiota including Clostridium cluster IV, *Faecalibacterium prausnitzii*, Rosburia spp., Lactobacillus spp., Bifidobacteria spp., *Akkermansia muciniphila*, *Bacteroides fragilis*, and Ruminococcus spp. and the *Firmicutes* to *Bacteroidete*s ratio.

To examine gut microbiota and fecal calprotectin and lactoferrin, stool samples (10 g) from one defecation will be taken from each individual at study baseline and end of trial. The samples will be immediately stored at − 20 C° until further analysis. Bacterial DNA will be extracted using the QIAamp (QIAGEN) commercial fecal DNA kit. Calprotectin is a calcium binding protein commonly derived from neutrophils and monocytes and in to a lesser extent from macrophages [15]. Calprotectin is found in stool and plasma, and its concentration increases throughout inflammatory conditions including IBD, and infection [15, 16]. The quantity of intestinal microbiota including Clostridium cluster IV, *F. prausnitzii*, Rosburia spp., Lactobacillus spp., Bifidobacteria spp., *A. muciniphila*, *B. fragilis*, and Ruminococcus spp., as well as the *Firmicutes* to *Bacteroidetes* ratio, will be determined using commercial real-time PCR kits (QIAamp, QIAGEN). In addition, fecal concentrations of calprotectin and lactoferrim will also be measured using an enzyme-linked immunosorbent assay. Therefore, our primary outcomes will be the mean difference in changes from baseline to 4-week follow up in calprotectin concentrations and quantity of gut microbiota between the intervention and control groups.

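### The sample-size inputs are labelled as mean fecal calprotectin but are most naturally changes from baseline; on that reading 15 per arm gives about 65–70% power, not 80%

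*Protocol article*

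**What the plan says.** The Study sample size calculation section sizes the trial for 80% power at a two-sided 5% level. It names the target as the "expected difference between the intervention and control groups in mean fecal calprotectin" and gives the inputs as "S1= 25.88, S2= 21.99, μ1= 26.6, μ2= 4". The section does not say whether these are levels or changes, and both means are printed without a sign. It then reaches 15 per group after "allowing for 10% drop-out in each group".

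The Primary outcomes section puts the outcome on another scale: "the mean difference in changes from baseline to 4-week follow up in calprotectin concentrations", compared between the arms. The same section says how calprotectin is obtained: "fecal concentrations of calprotectin and lactoferrim will also be measured using an enzyme-linked immunosorbent assay". A single measurement is therefore a concentration and cannot be below zero, whereas a change from baseline can.

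**The concern.** The label in the sample-size section does not match the outcome definition, and the numbers do not fit the label. An SD more than five times the mean is not what a set of non-negative concentrations looks like, least of all one to be compared by a t test. It is unremarkable for a change score centred near zero.

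The power statement is the article's only account of what the trial can detect on calprotectin. If readers cannot tell whether 22.6 and the two SDs refer to levels or to changes, they cannot set a null or positive result on the change outcome against the stated 80%. The SD of a level and the SD of a change are in general different quantities, so the distinction can alter the power.

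**Working it through.** **Inputs.** From the Study sample size calculation section: S1 = 25.88, S2 = 21.99, μ1 = 26.6, μ2 = 4, two-sided α = 0.05, power 80%, drop-out 10%, 15 per group. From the Primary outcomes section: the outcome is change from baseline to week 4, and calprotectin is an assayed concentration.

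**1. Reproducing the plan's figure.** The printed denominator is μ1² − μ2².

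- (1.960 + 0.842)² = 7.849
- S1² + S2² = 25.88² + 21.99² = 1153.33
- μ1² − μ2² = 26.6² − 4² = 691.56
- n = 7.849 × 1153.33 / 691.56 = 13.09
- With drop-out: 13.09 / 0.9 = 14.5, rounded up to 15

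The stated 15 per group reproduces from the formula as printed.

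**2. Can the second pair be concentrations?**

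- Ratio of SD to mean: 21.99 / 4 = 5.50.
- In a sample of n non-negative values the SD cannot exceed mean × √n. The pair therefore needs n ≥ (21.99 / 4)² = 30.2, that is at least 31 values, nearly all at or close to zero. At n = 30 the largest possible ratio is √30 = 5.48; at n = 15 it is √15 = 3.87, an SD of at most 15.5.
- Under a normal model the proportion below zero is Φ(−4 / 21.99) = 43%. For the first pair it is Φ(−26.6 / 25.88) = 15%.

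As levels the second pair is not credible. As changes, both pairs are ordinary.

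**3. Power if the inputs are changes of the same sign.** No input alters; only the denominator is corrected to (μ1 − μ2)².

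- Difference: 26.6 − 4 = 22.6, and 22.6² = 510.76
- n = 7.849 × 1153.33 / 510.76 = 17.72, so 18 evaluable per arm; 18 / 0.9 = 20 after drop-out
- Root-mean-square SD: √(1153.33 / 2) = 24.01; standardised difference 22.6 / 24.01 = 0.94

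Power of the two-sided t test (noncentral t):

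| Evaluable per arm | Power |
|---|---|
| 13.5 (15 less 10%) | 65% |
| 15 | 70% |

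**4. Power if the source shows end-of-study values.** The SD of change is then 24.01 × √(2(1 − r)), where r is the correlation between baseline and week 4. This assumes the same SD at both times. The article gives no r, so the values below are assumptions.

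| r (assumed) | SD of change | Power, 13.5 to 15 per arm |
|---|---|---|
| 0.3 | 28.41 | 51–56% |
| 0.5 | 24.01 | 65–70% |
| 0.7 | 18.60 | 86–89% |
| 0.8 | 15.19 | 96–98% |

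At r = 0.5 the factor √(2(1 − r)) equals 1, so the answer is the same as in step 3.

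**The case against.** The best reply is that the argument supports the plan's choice of scale. If the figures are not levels they are changes, and change is the scale of the primary outcome. All that is missing is the word change, and with it added neither the inputs nor the required n move. This stands. A reader might infer that the 80% power has been shown to have nothing to do with the primary outcome; the article does not support that. The link is undocumented.

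A second reply is that the inputs may come from a larger external sample, so a bound computed at 15 per arm does not rule them out as levels. This also stands: impossibility is strict only for 30 or fewer values. Beyond that the correct statement is that they are not credible as levels, and certainly not as normally distributed ones.

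Third, a reader might present the power as unknown over a very wide interval, by combining low assumed correlations with a sign dropped from one mean. Nothing in the article says a sign was dropped, and the range of r is arbitrary. On the natural reading the fall from 80% to 65–70% is due wholly to the printed denominator, and the label adds nothing to it.

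Fourth, in a randomised comparison the difference in week-4 means and the difference in mean changes have the same expectation. The target of 22.6 therefore remains meaningful on either reading; only the SD is in doubt. This too is correct.

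Finally, unit, source and arm of planning values are details that an article may leave to the full protocol. Their absence alone is no finding. What remains is a printed label that conflicts with the printed outcome and with the printed numbers, together with a power figure that those numbers do not deliver.

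**Conclusion.** The point holds as a labelling error with a consequence for the stated power. The sample-size section describes its inputs as calprotectin means, the outcome is a change, and mean 4 with SD 21.99 is not believable for a concentration. The most natural reading is mean changes with SDs of change. On that reading, with both changes of the same sign as printed, power for a difference of 22.6 is about 65–70% with 13.5 to 15 evaluable per arm, not 80%.

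That figure assumes approximately normal changes, a two-sided 5% t test and the printed SDs. It is the same shortfall that the denominator error produces, so it should be counted once. The article does not establish that the inputs are changes, so the reading is an inference and the authors must confirm it.

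**What to change.** In the Study sample size calculation section, check the source of the four figures. If they are changes, label them as mean changes in fecal calprotectin from baseline to week 4 with SDs of change, and give the sign of each mean. In the same edit, replace the denominator by the square of the difference between the means and restate the power for the primary outcome: about 65–70% with 13.5 to 15 evaluable per arm if the difference is 22.6. If the signs turn out to give another difference, recompute from that one.

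Only if the source shows that they are end-of-study values, use an SD of change under a stated, assumed correlation and report the power as a range.

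Keep 15 per arm; the Trial status section reports recruitment as complete. The cost is one corrected paragraph and a less favourable stated power. No further patients are needed and the analysis does not change.

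### The sample-size formula divides by the difference of the squared means instead of the squared difference, so 15 per group gives about 63–70% power, not 80%

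*Protocol article*

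**What the plan says.** The protocol article justifies its size in one place, the section Study sample size calculation. It sets a "type I error of 5% (α = 0.05" level and a "type II error of 20% (β = 0.20, power = 80" per cent requirement. The endpoint is the "expected difference between the intervention and control groups in mean fecal calprotectin", and the sample size is described as "calculated based on the two sided *t* test".

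The inputs are "S1= 25.88, S2= 21.99, μ1= 26.6, μ2= 4". The displayed formula multiplies (Z for 1 − α/2 plus Z for 1 − β)² by S1² + S2² and divides by μ1² − μ2².

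The conclusion is: "Based on this formula and allowing for 10% drop-out in each group, we will need a sample size of 15 persons for each group". The abstract and the Study design section carry the same 15 per group, 30 in all.

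**The concern.** The sample size for comparing two means depends on how far apart the means are, so the denominator must be the square of their difference. The difference of their squares is another quantity. It depends on the level of the means as well as on the gap between them, and it is larger than the squared difference here, which makes the required number too small.

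Fecal calprotectin is a primary outcome and the only one used to size the trial. If the stated power is wrong, a null calprotectin result will be read against a false-negative risk of 20% that the design does not provide. The first question is whether the formula was misprinted or actually used.

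**Working it through.** **Inputs**, all from Study sample size calculation: two-sided α = 0.05 (Z = 1.960), power 80% (Z = 0.842), S1 = 25.88, S2 = 21.99, μ1 = 26.6, μ2 = 4, drop-out 10% per group. The Statistical analysis section names the independent-sample t test for normally distributed outcomes.

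**Numerator, common to both versions**
- (1.960 + 0.842)² = 7.849 (unrounded Z values)
- S1² + S2² = 669.77 + 483.56 = 1153.33
- Product: 9052.4

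**Printed denominator: reproducing the plan's figure**
- 26.6² − 4² = 707.56 − 16 = 691.56
- n = 9052.4 / 691.56 = 13.09
- Drop-out: 13.09 / 0.9 = 14.54, rounded up to **15**. Multiplying instead, 13.09 × 1.1 = 14.40, also rounds up to 15.

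**Correct denominator**
- (26.6 − 4)² = 22.6² = 510.76
- n = 9052.4 / 510.76 = 17.72, so **18 evaluable** per group
- Drop-out: 18 / 0.9 = **20 enrolled** per group
- On the t distribution: 19 evaluable (power 80.6%; 18 gives 78.3%), and 19 / 0.9 = 21.1, so 22 enrolled.

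**Why the printed form is not a valid variant.** Add 10 to both means. The difference is still 22.6, but the printed denominator becomes 36.6² − 14² = 1143.56 and n falls to 9052.4 / 1143.56 = 7.9.

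**Power at the planned size.** The root-mean-square SD is √(1153.33 / 2) = 24.01, so d = 22.6 / 24.01 = 0.94. For the t test, the noncentrality is 22.6 / √(1153.33 / n) on 2n − 2 degrees of freedom.

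| Evaluable per group | Power, two-sided t test | Power, normal approximation | Difference detectable at 80% power (t test) |
|---|---|---|---|
| 15 | 70.1% | 73.2% | 25.4 |
| 14 | 66.9% | 70.2% | 26.4 |
| 13 | 63.4% | 67.0% | 27.5 |

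Ten per cent of 15 is 1.5, so the planned drop-out falls between the last two rows; at 13.5 the t-test power is 65.2%. Allowing for unequal variances (Welch) changes these figures by about 0.1 percentage point.

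**The case against.** **Another route to about 15.** The correct denominator with a one-sided α of 0.05 gives 13.96, or 14 evaluable per group. Multiplied by 1.1 that is 15.4, which could be written as 15. The printed formula, if rounded up to 14 before dividing by 0.9, gives 15.6 and hence 16. So the wrong denominator is not strictly the only path to 15. But the section says the test is two-sided, prints Z for 1 − α/2, and attributes 15 to the displayed formula. That formula gives 15 directly when the rounding is done once, at the end. The one-sided reading contradicts the text.

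**Other sources of power.** Study design randomises within matched pairs, and Statistical analysis adds multivariable regression. Either could change the power. But the sample-size section takes no credit for them, the named test is unpaired, and the article gives no correlation from which a gain could be computed. They do not make the stated derivation right.

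**Which drop-out case.** The 63% figure is for 13 completers, a loss of 13.3%; exactly 10% gives about 65%. This is fair, and 63% is best read as the round-down end of the range. On the normal approximation that the formula uses, the range is 67–73%, still well short of 80%.

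**What the fix changes.** Recruitment is reported as complete, so allocation, endpoint, test and type I error stay as they are. That limits the remedy, but the power claim for a primary outcome is still wrong.

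**Conclusion.** The concern holds. The denominator is wrong, and the wrong denominator reproduces the stated 15 per group. On the plan's own inputs, 80% power needs 18 evaluable and 20 enrolled per group by the normal formula, or 19 and 22 by the t test. The planned 15 per group gives about 70% power if everyone completes and about 63–67% after drop-out of roughly 10%.

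These power figures are for a two-sided, unadjusted, unpaired t test at a true difference of exactly 22.6 with SDs of 25.88 and 21.99. They also assume that those values describe the endpoint to be analysed. The section does not say whether they are changes from baseline, whereas Primary outcomes defines the calprotectin outcome as a change. The formula error does not depend on any of these assumptions.

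**What to change.** - Correct the denominator to (μ1 − μ2)² and show the resulting 18 evaluable and 20 enrolled per group (19 and 22 if the t distribution is used).
- Replace the 80% claim with the power for the number actually randomised. Trial status says recruitment is complete but gives no enrolled number. If it was 15 per group, state about 70% with no losses and about 63–67% with 13 or 14 completers, for a difference of 22.6.
- State the difference detectable at 80% power: 25.4 with 15 per group, 27.5 with 13.
- State whether the means and SDs are changes from baseline, so that the calculation matches the primary outcome.

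The cost is one formula and one paragraph. No patients are added and the analysis is unchanged; the stated power becomes less favourable.

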### Statistical analysis

Normality of data will be examined using the Kolmogorov-Smirnov test. Continuous variables will be compared between the two groups by the independent sample *t* test, whereas the chi-square test will be used to compare categorical variables. Normally distributed continuous variables will be reported as mean ± SD, and as median and IQR if they are not normally distributed; categorical data will be reported as absolute and relative percentage frequencies. The effect of the study intervention on desirable outcomes will be measured using the independent sample *t* test for normally distributed data and the Wilcoxon test for non-normally distributed data. We will adjust our final results for potential confounding factors using multivariable regression modeling. Statistical analyses will be done using SPSS, version 21. *P* values <0.05 will be considered statistically significant.

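### The primary test is left to a Kolmogorov-Smirnov result at 15 per arm, and the unadjusted comparison of raw changes loses power if the biomarkers are skewed

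*Protocol article*

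**What the plan says.** The Statistical analysis section of the protocol article sets a two-step rule. First, "Normality of data will be examined using the Kolmogorov-Smirnov test". The effect of the diet is then tested by the independent-samples t "test for normally distributed data and the Wilcoxon test for non-normally distributed data". No transformation is mentioned. The section adds that final results will be adjusted by multivariable regression, but names neither the covariates nor the scale of the outcome.

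The Primary outcomes section lists fecal calprotectin and lactoferrin, eight bacterial groups and the Firmicutes to Bacteroidetes ratio; the bacterial measures "will be determined using commercial real-time PCR kits". It closes by defining the primary comparison as the between-arm difference in mean change from baseline to week 4 for calprotectin and the bacterial quantities. The Secondary outcomes section does the same for hs-CRP, TNF-α and IL-1β.

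**The concern.** Two separate matters arise.

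The first is that the test is chosen by the data, separately for each outcome. If the gate passes, the analysis addresses a difference in means. If it fails, the analysis is a rank test, which does not estimate that quantity. The target of the primary analysis then depends on a normality test run on about 15 patients per arm. The word Wilcoxon also leaves open a rank-sum or a signed-rank test. The distinction matters because the Study design section randomizes within 15 matched pairs.

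The second is efficiency. Concentrations, PCR quantities and ratios cannot fall below zero and may well be right-skewed. Differences of raw values are then driven by the few patients with high values, and without the baseline value as a covariate some precision is lost as well. A trial of 30 patients has little power to spare.

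**Working it through.** **Inputs from the documents** (Study sample size calculation): two-sided α = 0.05, power 80%, "S1= 25.88, S2= 21.99, μ1= 26.6, μ2= 4", and "allowing for 10% drop-out in each group, we will need a sample size of 15 persons for each group".

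**The plan's own figure.** As printed, the formula gives (1.960 + 0.842)² × (25.88² + 21.99²) / (26.6² − 4²) = 9,052 / 691.56 = 13.09. Then 13.09 / 0.9 = 14.5, so 15 per group, as stated. The printed denominator is a difference of squares; with (26.6 − 4)² = 510.76 the result is 17.7, so 18, or 20 after drop-out. That is a separate error and is not relied on here.

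**Assumptions, none of them in the documents.** Baseline and week-4 values are lognormal with log SD σ and correlation 0.5. For σ: if 26.6 and 25.88 describe levels (the text does not say, and gives no units), the coefficient of variation is 25.88 / 26.6 = 0.973 and σ = √ln(1 + 0.973²) = 0.82. A range of 0.5 to 1.2 is shown around it. The diet lowers the log week-4 value by 1.07 × √(1 − 0.5²) × σ = 0.927σ, chosen so that ANCOVA on logs has about 80% power. The corresponding ratios of geometric means are exp(−0.927σ) = 0.63, 0.47 and 0.33 at σ = 0.5, 0.82 and 1.2.

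**Rule simulated.** Kolmogorov-Smirnov on raw changes in each arm; t test if both arms pass, otherwise rank-sum. The protocol does not say whether the Lilliefors correction applies, so both versions were run (20,000 replicates, 15 per arm).

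| Log SD | Planned rule, Lilliefors | Planned rule, uncorrected | Rank-sum on raw changes, no gate | t test on log change | ANCOVA on logs |
|---|---|---|---|---|---|
| 0.5 | 53% | 51% | 52% | 69% | 80% |
| 0.82 | 44% | 38% | 45% | 70% | 80% |
| 1.2 | 39% | 30% | 39% | 69% | 79% |

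**Where the loss arises.** With Lilliefors, the rule has almost the same power as a rank-sum test with no gate (44.4% against 45.2% at σ = 0.82), so the gate itself costs under one point. Uncorrected, it costs 45.2 − 38.2 = 7.0 points at σ = 0.82 and 39.4 − 30.3 = 9.1 points at σ = 1.2. Moving to log change at σ = 0.82 gains 69.6 − 44.4 = 25.2 points over the Lilliefors rule, and adding the baseline covariate gains a further 79.6 − 69.6 = 10.0.

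A second scenario (σ = 1.0, correlation 0.6, 60% reduction) shows the same pattern: planned rule 39% uncorrected or about 47% with Lilliefors, ungated rank-sum about 48%, ANCOVA on raw values about 60%, t test on log change about 77%, ANCOVA on logs about 84%.

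**How the gate behaves.** At n = 15, a lognormal arm with σ = 0.5, 0.82 or 1.2 is flagged in 26%, 53% and 77% of samples with Lilliefors, and in 0.3%, 3% and 13% without. Applied to raw changes at σ = 0.82, both arms pass, so the t test is used, in 34% of trials with Lilliefors and 94% without. In the second scenario the t and rank-sum tests disagreed on significance in about 19% of trials.

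**Bounds.**
- Type I error of the two-stage rule is 3.9% to 5.0%.
- If changes are normal with the protocol's own means and SDs, the rule gives 70.0% and the t test alone 70.3%.
- With 13 evaluable per arm (15 × 0.9 = 13.5) and σ = 0.82, power is 38% (Lilliefors) or 33% (uncorrected), against 72% for ANCOVA on logs.
- If week-4 values rather than changes were tested, the rule would keep 0.92 to 0.97 (Lilliefors) or 0.77 to 0.93 (uncorrected) of the power of a log-scale t test. The Primary outcomes section specifies changes.

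**The case against.** A t test with a rank fallback is common in a condensed protocol article, and transformations and covariates are often left to an analysis plan, which is not shown. That excuses silence on detail. It does not excuse the rule that is stated, nor its mismatch with the stated outcome.

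A reader might infer that the pre-test itself roughly halves power. The documents and the calculation do not support that. With Lilliefors, removing the gate and keeping a rank test would recover almost nothing. ANCOVA on logs also differs from the plan in two respects, scale and baseline adjustment, so the whole gap cannot be charged to either one.

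Nor do the documents establish halving as a fact about this trial. They state no skew, no log SD, no correlation and no multiplicative effect. At log SD 0.5 the loss is about one third (53% against 80%), and with normal changes it is nil. The figures are for a reduction; for an increase by the same ratio the loss on raw changes is smaller.

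It would also be too strong to say that the normality test cannot see skew: with Lilliefors it flags half or more of lognormal arms at log SD 0.82 and above.

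The planned multivariable regression might include baseline and so recover some power. On raw values it would recover only part (about 60% against about 84% in the second scenario), and its scale is not given. Finally, ratios of geometric means are one defensible target among several. What stands is that one target must be chosen beforehand, and the stated rule does not do so.

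**Conclusion.** The point holds in two parts. From the text alone, the primary test is not fixed, and one of its two branches does not estimate the stated primary quantity. Conditionally on skewed data, the unadjusted comparison of raw changes is inefficient: about 30% to 53% power where log-scale ANCOVA has about 80%, given lognormal values, log SD 0.5 to 1.2, correlation 0.5, a multiplicative reduction and 15 per arm. That loss is due mainly to the raw change scale and the missing baseline covariate. Validity is not threatened, since type I error stays at or below 5%. This should be changed, but it does not invalidate the trial.

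**What to change.** For the primary and secondary biomarkers:

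- Drop the normality gate.
- Pre-specify as the main analysis an ANCOVA of log week-4 value on log baseline value, reporting the ratio of geometric means with its 95% CI.
- Restate the outcome definitions in the Primary and Secondary outcomes sections to match.
- Keep one named rank test, the between-group rank-sum, as a sensitivity analysis only.
- State a rule for zero or below-detection values, which cannot be logged as they stand.

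The cost is wording: baseline and week-4 samples are already planned, so no new data are needed. The change should be dated before outcome data are examined by arm. The small downside is that effects are reported as ratios rather than absolute mean differences.

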### Study design

The study was designed according to the Standard Protocol Items: Recommendations for Interventional Trials (SPIRIT) 2013 checklist. After recruitment, participants will enter into a 2-week run-in period, during which general information on diet, physical activity, type and dosage of medications will be obtained. All measurements, including anthropometric and biochemical assessments, will be made at this stage, and then participants will be stratified based on age (20–40 and 40–60 years), gender (male/female), body mass index (18.5–24.9 and 25–30), and type of medicines (anti-inflammatory and immunosuppressant) into different strata. Actually, first we will enroll a participant who meets the inclusion criteria in a stratum. Then, based on these variables the second person, who is matched with the first one in that stratum would be gone to the same stratum. So, we would have two similar persons (in terms of the aforementioned variables) in a stratum. Then, the two persons in a single stratum would be randomly assigned into the intervention and non-intervention groups. Therefore, we would have 15 strata (each consisting of two similar persons) in total and then individuals in the strata would be randomly allocated to the aforementioned groups. So, we would have 15 people in each group and the groups would be almost similar in terms of these variables. A person who is not part of the study will randomly allocate participants. Participants in the intervention group will receive a low-FODMAP diet according to their usual dietary intakes, whereas participants in the control group will receive their usual diet without any modification, for 4 weeks. Participants in both groups will receive the usual dietary recommendations for patients with IBD. To evaluate participants’ compliance, three 24-h dietary recalls will be taken throughout the intervention. Participants will be asked not to change their life-style and medicines during the study. Again, all measurements will be examined at the end of trial.

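### The intervention effect is tested by an unadjusted two-sample test on change scores although every outcome's baseline is collected; adjusting for baseline would gain precision at almost no cost

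*Protocol article*

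**What the plan says.** The Primary outcomes section of the protocol article has stool taken from each participant at baseline and at the end of the trial. It concludes: "our primary outcomes will be the mean difference in changes from baseline to 4-week follow up in calprotectin concentrations and quantity of gut microbiota", compared across the two arms. The Secondary outcomes section treats the serum markers in the same way.

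The Statistical analysis section then states: "The effect of the study intervention on desirable outcomes will be measured using the independent sample" t test for normally distributed data, with the Wilcoxon test as the alternative for non-normal data. It adds: "We will adjust our final results for potential confounding factors using multivariable regression modeling". That sentence neither includes nor excludes the baseline value of the outcome, and it does not make the adjusted model the primary result.

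The sample-size section rests on the same two-sample comparison ("calculated based on the two sided" t test). Its numerical inputs are "S1= 25.88, S2= 21.99, μ1= 26.6, μ2= 4", and it ends: "Based on this formula and allowing for 10% drop-out in each group, we will need a sample size of 15 persons for each group".

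**The concern.** A change score subtracts the whole baseline value, which is the same as fixing the slope of week 4 on baseline at 1. When the true slope is below 1, this over-corrects. It adds noise, and it carries part of any chance baseline difference into the treatment estimate. A model that estimates the slope avoids both.

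This matters more in a small trial. Participants are matched on age, gender, BMI and type of medicine, not on calprotectin or bacterial quantities, so sizeable chance differences in those baselines are likely. Recruitment is reported as complete, so the choice of analysis is one of the few ways left to gain precision without more patients.

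**Working it through.** **1. The planned figure.** Inputs from the sample-size section: α = 0.05 two-sided, power 80%, S1 = 25.88, S2 = 21.99, μ1 = 26.6, μ2 = 4, drop-out 10%.

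- (1.960 + 0.842)² = 7.849; S1² + S2² = 669.77 + 483.56 = 1153.33.
- The printed denominator is a difference of squares: 26.6² − 4² = 691.56. So n = 7.849 × 1153.33 / 691.56 = 13.09, and 13.09 / 0.9 = 14.54, giving the stated 15.
- The standard denominator is the squared difference: 22.6² = 510.76. So n = 17.72, rounded up to 18, and 18 / 0.9 = 20 per group.

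The shortfall in power therefore arises in the formula, before any choice of test.

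**2. Power of the planned t test.** Pooled SD = √(1153.33 / 2) = 24.01; standardised difference = 22.6 / 24.01 = 0.94. With the noncentral t on 2n − 2 degrees of freedom, power is 70.1% at 15 per arm, 66.9% at 14 and 63.4% at 13. The planned drop-out leaves 15 × 0.9 = 13.5 per arm on average.

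**3. Gain from adjusting for baseline.** Let σ be the SD of the outcome at each visit (assumed equal) and ρ the baseline to week-4 correlation. Change-score variance is 2σ²(1 − ρ) and the residual variance of the adjusted model is σ²(1 − ρ²), so the ratio is (1 + ρ)/2: 0.65, 0.75 and 0.85 at ρ = 0.3, 0.5 and 0.7. The protocol gives no ρ; this range is an assumption.

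Reading the SDs as SDs of change, the residual SD is 24.01 × √((1 + ρ)/2) on 2n − 3 degrees of freedom. The first adjusted figure in each cell treats the arms as balanced at baseline. The second averages over chance baseline imbalance, which inflates the variance of the adjusted estimate.

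| Completers per arm | Planned t test | ρ = 0.3 | ρ = 0.5 | ρ = 0.7 |
|---|---|---|---|---|
| 15 | 70% | 87 / 86% | 82 / 80% | 77 / 75% |
| 14 | 67% | 84 / 83% | 79 / 77% | 74 / 72% |
| 13 | 63% | 81 / 80% | 76 / 74% | 70 / 68% |

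**4. Where the gain ends.** Averaged over chance imbalance, the inflation factor is 1 + 1/(2n − 4), or 27/26 at 15 per arm. The adjusted model loses its advantage when (1 + ρ)/2 exceeds 26/27, that is, when ρ is above about 0.93.

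**5. If the SDs are of levels instead.** The change SD becomes 24.01 × √(2(1 − ρ)) and the adjusted residual SD 24.01 × √(1 − ρ²). At 15 per arm (balanced-baseline calculation) and ρ = 0.3, 0.5 and 0.7, the change-score t test has 55.7%, 70.1% and 89.5% power; the adjusted model has 74.0%, 81.8% and 93.5%. The direction is the same and the sizes differ. A mean of 4 with an SD of 21.99 is hard to reconcile with a non-negative concentration, which favours the change reading but does not settle it.

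**6. Chance imbalance.** With 15 per arm the standard error of a baseline difference is √(2/15) = 0.37 SD. Under simple randomisation a gap above 0.5 SD has probability 2 × (1 − Φ(0.5/0.365)), about 17% for each outcome. Given a baseline gap δ, the change-score estimate is shifted by −(1 − ρ)δ.

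**The case against.** The strongest reply is that nothing here is an error. Under randomisation a two-sample test on change is unbiased and valid, and it agrees with the stated endpoint and with the test used for sizing. That stands: chance imbalance affects the estimate conditionally and costs precision, but it does not invalidate the plan. The point is one of efficiency.

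A reader might infer more than the documents support in four ways.

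- **That adjustment restores 80% power.** This would need a favourable ρ, SDs that are of change, and little drop-out. The protocol gives neither ρ nor the meaning of the SDs, and it plans for 10% drop-out. At ρ = 0.7 power is below 80% even with all 15 per arm. The shortfall itself belongs to the sample-size formula.
- **That the primary test is simply a t test.** The plan has a Wilcoxon branch for non-normal data. The power figures above do not apply to outcomes that take it, and a replacement model on the raw scale would drop that safeguard.
- **That the regression for confounders is an after-the-fact adjustment, or is deficient because its covariates are unnamed.** It is stated in advance, and a list of covariates is detail that an article commonly leaves to the full protocol or analysis plan. It may well include baseline; the text does not say.
- **That a change score is always at least as noisy.** In a sample this small that fails when ρ is very high.

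**Conclusion.** The point holds as a recommendation to improve efficiency. The stated effect test does not use baseline as a covariate although baseline is collected from everyone, and for all but very high ρ a baseline-adjusted model is more precise and removes the shift due to chance baseline imbalance.

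As an illustration, if the SDs are of change and ρ is 0.3 to 0.7, power goes from about 70% to about 75–87% with 15 completers per arm, and from about 63–67% to about 68–84% with 13 or 14. The direction is well supported; the size is only as good as those assumptions. The gain partly offsets the power lost through the difference-of-squares denominator and does not replace correcting it.

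**What to change.** Before outcome data are examined, state as the primary analysis of each outcome a linear model of the week-4 value on treatment group and that outcome's own baseline value. Report the adjusted difference with its 95% confidence interval. Fit it on the log scale where the outcome is skewed, as is likely for calprotectin and the bacterial quantities; the effect is then a ratio of geometric means. Use the same model for the secondary outcomes. Keep the planned t test or Wilcoxon test on change as a sensitivity analysis, and label the regression for other confounders as supportive.

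The cost is a change of wording. No new data are needed, and the model can be fitted in the SPSS package already named. The baseline covariate uses one degree of freedom. Terms for the matching variables or pairs would use more and are not allowed for in the power figures above.
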